**Fig. 1 Fig1:**
[figure not shown]
Recruitment

The intervention, see Fig. 2, is delivered by a nurse with a Master of Science in nursing degree who has been working as an registered advanced practice nurse [31, 38]. At weekly 1 hour meetings, of the Research Intervention Team with the specialist in internal medicine who focuses on geriatrics and the principal investigator, the intervention nurse reflects on her training, consulting and support experience. The intervention consists of two parts, which are described in detail below:

**Fig. 2 Fig2:**
[figure not shown]
Intervention 1 and 2

Intervention 1 – pain assessment

Aim: to reinforce the systematic pain assessment of healthcare workers.Encourage training of healthcare workers on pain assessment using the BESD instrument (assessment of pain in dementia of the German Pain Society) by the intervention nurse [39–41].Individual coaching of healthcare workers (2× per healthcare worker at bi-weekly intervals) on the correct use of the BESD in everyday clinical life in nursing homes and a systematic and structured communication among healthcare workers and between healthcare workers and physicians based on ISBAR [42] and SOAPIER [43]. ISBAR is clinical communication technique (ISBAR: identify, situation, background, assessment, recommendation). SOPIER is a problem-oriented technique whereby the nurse identifies and lists the patient’s health concerns (SOPIER: subjective data, objective data, assessment data, plan, intervention, evaluation, recommendation).

Intervention 2 – pain management

Aim: to reinforce the systemic pain management skills of healthcare workers including systematic documentation and information among nursing staff and general practitioners.Provide individual support and advice to healthcare workers on how to develop a Pain Action Plan in order to implement assessment and management and to evaluate them for each person affected with dementia suffering from pain or suspected pain.Zwakhalen, Hof, Hamers [44] concluded that the presence of pain should be assumed at a BESD value of two or higher. However, even at values of zero point on the BESD scale the presence of pain cannot be ruled out with certainty only because the person in question shows no discernible pain behaviour. That is why a professional exchange of information among nurses is vital for different pain management strategies to be tested in case of suspected pain or pain following a “trial and error” approach in consultation with the attending physician, if necessary, and to assess the success or failure of these strategies. Accordingly, there is a need for systematic observation by staff members who will be specifically trained for this task in intervention 1.Discussions with healthcare workers based in a hospital ward and the intervention nurse on issues in the implementation of individual Pain Action Plans and strategies. The older person’s reference nurse calls for a meeting with members of the nursing team, the attending physician and the intervention nurse when she has uncertainties, in the care of newly admitted older person, in case of suspected pain or in case of changes to the older person’s therapy.

Sustainability and veracity of the interventions are ensured by following the comprehensive evaluation process based on Dobbins [45] that consists of:assessment of the accuracy between the conducted intervention and the study protocol: 50% of the intervention protocols are tested for compliance with the study protocol based on selected pain management strategies and structured communication skills (ISBAR, SOPIER, prompt initiation of medical prescriptions, usage of non-analgesic pain management strategies) by descriptive analysis.evaluation of operating procedures that are associated with pain managementquestioning of acceptability of the interventions carried out for all health care workers with a scale from 0 (= no acceptance) to 10 (= fully accepted)compliance (adherence) of interventions for all health care workers with a scale from 0 (= no adherence) to 10 (= complete adherence)assessment of the potential for change in clinical practice among healthcare workers with a scale from 0 (= no conversion potential) to 10 (= complete transformation possible)assessment of potential change in the management of pain among health care workers with a scale from 0 (= no change in potential) to 10 (= comprehensive amendment potential)

Pain as primary outcome is measured in all people with dementia in the comparison and intervention groups by means of:pain events per shift and per week;degree of pain intensity per work shift, per week day;pain-free intervals.

Secondary outcome variables will be measured by:frequency of behavioural problems (Neuropsychiatric Inventory NPI [46]);number/dosages of psychotropic drugs;Number/dosages of analgesics.

The documentation regarding the assessment of pain by nurses is always done in duplicate, by a health care worker on different education level. Tertiary outcome variables will be measured by:changes in the assessment of pain by healthcare worker on healthcare assistant level andchanges between the two healthcare worker groups on healthcare assistant level and registered nurse level.

Hypotheses for primary outcomes are:H_a1_: There is a 20% reduction in pain events over time before and after the intervention and between intervention and comparison groups among nursing home older people.H_a2_: There is a 50% reduction in pain intensity over time before and after the intervention and between intervention and comparison groups among older people.H_a3_: There is a 20% reduction in the duration of pain free intervals over time before and after the intervention and between intervention and comparison groups among older people.

Furthermore the following hypotheses will be explored:There is a difference in the behavioural problems score (NPI) before and after the intervention and between intervention and comparison groups among older people.There is a difference in the psychopharmacological drug numbers/dosage before and after the intervention and between intervention and comparison groups among older people.There is a difference in the numbers/dosage of painkillers before and after the intervention and between intervention and comparison groups among older people.There is a difference in pain assessment over time before and after the intervention and between intervention and comparison groups among nursing home older people.There is still a difference in pain assessment by healthcare workers on assistant level over time before and after the interventionThere is still a difference in pain assessment between healthcare workers on assistant level and registered nurses level over time before and after the intervention.

The sample size used in the trial is determined based on the requirements of event history analyses and multilevel analyses to test the mentioned hypotheses.

Event history analyses: The required number of events for a two-tailed test of individual coefficients within a Cox model with other covariates has been calculated based on the method of Hsieh and Lavori [41]. A total of *n* = 179 people and 121 events are required for a power of 0.8 and a significance level of 0.05 based on an expected hazard ratio of 0.6 (SD 0.5), a probability of occurrence of 0.75 and a drop-out rate of 10%. Both the number of people and the number of events determined in the intended study protocol can be collected.

Multilevel analyses (linear mixed models): The required number of cases for basic evaluations using multilevel models/linear mixed models have been determined by the approximation method [47] - with equal power and significance level as in the event analyses. This approach recognises a random intercept model with covariates that only vary between older people (treatment). In order to carry out only two repeated measurements per person, approximately *n* = 47 persons are required using a regression coefficient of 1 and a standard deviation of 0.5.

There are three data monitoring cycles (T0, T1, T2) and two intervention cycles (I1, I2) to measure the primary and secondary outcomes, see Fig. 3. Each data monitoring cycle extends over 7 weeks (=49 days) and includes seven different weekdays and at least three different work shifts. The data are extracted from the older people’ specific pain diaries (degree of pain intensity), which are kept separately from conventional nursing documentation. For the description of the sample, socio-demographic data on age and gender are collected from all participants. Additional data on qualifications and professional experience are collected from nursing staff, and care needs, dementia type and severity of dementia from people with dementia.

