**Methods:**

A quasi-experimental nurse-led intervention trial based on a convenience sample of four nursing homes in the Swiss Canton of Zurich examines the effects on dementia patients (*n* = 411), the healthcare institution and the qualification level of the healthcare workers compared to historical controls, using an event analysis and a multilevel analysis. Healthcare workers will be individually trained how to assess, intervene and evaluate acute and chronic pain. There are three data-monitoring cycles (T0, T1, T2) and two intervention cycles (I1, I2) with a total study duration of 425 days. There is also a process evaluation based on Dobbins analyses that analyse in particular the potentials for change in clinical practice of change agents.

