## Methods

We employ a quasi-experimental nursing-led intervention trial with a repeated measures design [36] based on a convenience sample of four nursing home clusters and a total sample of 411 dementia patients. All dementia patients in the comparison group will be obtained from the Zurich Life And Death with Advanced Dementia (ZULIDAD) Study [37]. The ZULIDAD data were collected from people with dementia (men and women), who are older than 70 years in one nursing home (*n* = 150), in 2015. Data between intervention sites and comparison site are similar because the same assessment instruments were used, based on an older person assessment instrument, and include pain duration, pain intensity, behavioural problems, differences of psychopharmacological drugs, and differences of analgesics. The comparison can be made with data from the first day and from the 49^th^ of each data collection phase (t0, t1, t2) and with a historical sample of pain duration and pain intensity from the last pain assessment documented in the older person Assessment Instrument Data (RAI) of each participant.

People with dementia in the intervention group will be are recruited in three healthcare institutions in the cantons of Thurgau and Zurich.

All healthcare workers from these three intervention institutions are included in the study, trained and coached in the provision of interventions. The following inclusion criteria apply to healthcare workers:must be at least 18 years old;must have been employed at least 12 months in the respective organisation;must work for at least 30% of a working week;be able to communicate in German.

The collection of data will take place in three nursing homes in the Canton of Thurgau and in the Canton of Zurich. For the comparison group, data from the ZULIDAD study [37] will be used.

All older people are screened for eligibility to participate in the study. Recruitment is described in Fig. 1. Only older people with documented nursing-initial-assessment symptoms of dementia are included in this intervention trial by author no. 3.

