**Fig. 3 Fig3:**
[figure not shown]
Time schedule

The actual data collection will be done by a study nurse with a BSc in Nursing. Potential confusions/problems with the raw data are discussed within the respective healthcare institution and with the leader of the study. Ambiguities with the procedure of data collection are discussed with the head of project management within the research team who also keeps a research diary. The study nurse transfers the anonymised data to the project management after the third measuring cycle. Two other study nurses enter the data into SPSS and carry out data cleansing before proceeding with the data analysis. The data of the comparison group are disclosed to the project management “PID” in encrypted form by the project manager “ZULIDAD”.

Data analysis will be performed using the IBM software programme SPSS® (version 24). The socio-demographic data are analysed descriptively (frequencies, central tendencies, standard deviations) and the outcome variables as follows:Pain intensity, duration and pain-free intervals are investigated in all dementia patients of the comparison and intervention group measuring the average duration of pain events per work shift (each work shift lasts 8.25 h) and per weekday, and the average degree of pain intensity per work shift, per work day as well as the duration of pain-free intervals with multilevel and events history analyses based on the data observation intervals T0, T1, T2.For the multilevel analyses (linear mixed models) over time, two levels are considered: the dementia patient and the healthcare institution. The event history analyses use cluster-adjusted Cox regressions. Furthermore, event history analyses will focus on evaluating the influence of the two nursing professional groups (at assistant/secondary and tertiary level), the pain pharmacotherapy (number and dosage), behavioural problems (NPI) and the psychopharmacotherapy (number and dosage).

A change in the assessment of pain by the healthcare workers is checked with interrater reliability tests. By means of the interrater reliability test, a potential variation between the two nursing groups on assistant/secondary and tertiary level is monitored.

To ensure the quality of data analyses, each data analysis step is independently checked by three different people.

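### With historical controls from one home, a before-after change over the 425 days cannot be separated from the intervention, and the article conflicts on which control data exist

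*Protocol article*

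**What the plan says.** The abstract of the Protocol article describes effects "compared to historical controls, using an event analysis and a multilevel analysis". The Methods section takes the whole comparison group from an earlier study: 150 people with dementia "who are older than 70 years in one nursing home", with data collected in 2015. The staff of all three intervention homes are trained and coached. Three monitoring cycles (T0, T1, T2) and two intervention cycles (I1, I2) fill 425 days.

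The first primary hypothesis is: "There is a 20% reduction in pain events over time before and after the intervention and between intervention and comparison groups". The hypotheses on pain intensity and on pain-free intervals have the same double form, over time and between groups.

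Three places bear on what pain data the comparison group has:

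- Methods, description of the comparison group: "The comparison can be made with data from the first day and from the 49^th^ of each data collection phase (t0, t1, t2"), and also with "a historical sample of pain duration and pain intensity from the last pain assessment documented" in the RAI for each participant.
- Methods, primary outcome list (after Fig. 2): pain is measured in both groups, as events per shift and per week, intensity per shift, and pain-free intervals.
- Methods, data analysis (after Fig. 3): pain in both groups is analysed "based on the data observation intervals T0, T1, T2".

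The only description of a treatment covariate in a mixed model is in the sample size paragraph: "This approach recognises a random intercept model with covariates that only vary between older people (treatment").

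**The concern.** The research question is causal: does the intervention reduce pain intensity and duration? Half of each primary hypothesis is a change from before to after the intervention. Over 425 days, pain in nursing home residents with dementia can change for other reasons, such as disease progression, ageing, season or unrelated changes in practice. Untreated homes followed over the same period, or homes that start at different times, would show how large that change is. The text describes neither. Controls observed in 2015 cannot show what happened during the trial's own period.

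The conflict over the control data adds to the problem. If each control has one RAI record, the between-group comparison can only compare levels. If the controls have a repeated course, a difference in change is possible, at least for the part of the drift that comes from ageing and disease. The reader cannot tell which applies, so cannot tell what the between-group half of each hypothesis will test.

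**Working it through.** **The plan's own figures.** The Cox sample size reproduces. With hazard ratio 0.6, covariate SD 0.5 (variance 0.25), two-sided 5% and power 0.8, events = (1.960 + 0.842)² / (0.25 × (ln 0.6)²) = 120.3, rounded up to 121. Then 121 / 0.75 / 0.9 = 179.3, against 179 stated. This point does not affect those figures. The plan states no expected change without intervention, so the drift below is an assumption.

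**What the two readings of the control data allow.** Take the fixed effects intercept, group, T1, T2, group × T1 and group × T2 (six parameters).

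- One observation per control: the columns for T1 and group × T1 are identical, and likewise for T2. The rank is 4 of 6, so time and intervention effects cannot be separated.
- Controls observed at three matching occasions: the rank is 6 of 6 and the terms are estimable. They carry a causal meaning only if the 2015 home would have drifted as the three intervention homes did.

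On the second reading the arithmetic works, but calendar-time changes remain unadjusted because the controls come from other years. Changes specific to a home also remain, because there is only one comparison home.

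**Effect of a drift on the before-after half.** Inputs: 411 − 150 = 261 intervention residents (documents); no intervention effect; drift d in SD units and correlation ρ between two occasions (both assumed); drop-out and clustering by home ignored.

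SE of the mean change = √(2(1 − ρ)/261). At ρ = 0.5 this is √(1/261) = 0.062 SD. The two-sided rejection probability is Φ(d/SE − 1.96) + Φ(−d/SE − 1.96).

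| Drift (SD) | d/SE at ρ = 0.5 | Rejection |
|---|---|---|
| 0.05 | 0.81 | 13% |
| 0.10 | 1.62 | 37% |
| 0.20 | 3.23 | 90% |

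At a drift of 0.10 SD:

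- ρ = 0.3: SE 0.073, rejection 28%.
- ρ = 0.7: SE 0.048, rejection 55%.

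**On the scale of the first hypothesis.** Suppose the intervention does nothing, both groups start at the same level (assumed) and pain events fall by 20% for other reasons. The before-after reduction is then 20%, and so is the gap between T2 and the historical level. Drift alone would give the hypothesised reduction in both contrasts.

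**The case against.** The strongest objection is to the broader claim, which a reader might infer from the last-RAI sentence, that the comparison group has no T0-T1-T2 course at all and a time effect is therefore not estimable. The article does not support that. The outcome list and the data analysis paragraph both include the comparison group. The sentence on the first and 49th days does not say which group it means, and the RAI record may be an additional source. The comparison study's own report and the time schedule in Fig. 3 are not shown. The rank of 4 holds only on the one-record reading. What the text does support is that these places conflict.

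A reader might also infer that the analysis model lacks a group-by-time term. The random-intercept sentence belongs to a sample size approximation. The data analysis paragraph names two levels and change over time without listing fixed effects, and a condensed article may leave those to an analysis plan. That inference is therefore not part of this point.

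Each hypothesis also requires a between-group reduction, so the rejection rates above describe only one half. That is correct. The second half is not a safeguard, though, since a level contrast with 2015 data can absorb the same drift.

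Finally, quasi-experimental studies commonly accept this limit. They may, but this article does not state it, and the Discussion does not mention time trends.

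**Conclusion.** The point holds in a limited form. Because the controls are historical and from one home, all three intervention homes are trained and no staggered start is described, a change during the 425 days cannot be attributed to the intervention on the design as written. This is true whichever account of the control data is right. Repeated 2015 records would narrow the gap for ageing and disease progression but would not close it.

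Under the stated assumptions the before-after half rejects about 13%, 37% or 90% of the time for drifts of 0.05, 0.10 or 0.20 SD, and 28–55% at 0.10 SD for correlations of 0.3 to 0.7. The size and direction of any real drift are unknown. An upward drift would mask a benefit.

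A reader might want a standard error or detectable difference for a controlled contrast. None should be quoted: with one comparison home, group-by-time cannot be told apart from home-by-time, so a figure based on resident numbers alone would mislead.

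**What to change.** 1. Reconcile the comparison-group description, the outcome list and the data analysis paragraph. State which pain records the comparison group has, how many per resident and at what interval.
2. If two or more comparable RAI pain records per resident can be obtained in both groups at a similar interval, make the between-group test for pain intensity and pain duration the group-by-time term (difference in change). State that it can adjust for ageing and disease progression, but not for calendar-time or home-specific changes.
3. Label the diary-based T0-T1-T2 change an uncontrolled before-after change, not the intervention effect. Apply the same label to any outcome without repeated control data, including pain events and pain-free intervals.

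Items 1 and 3 cost only wording. Item 2 needs a further extraction of routine records. These may not be accessible, since the control data come in encrypted form from another project; if they are not, item 3 applies to all primary outcomes. The price is lower precision for the controlled contrast and a more cautious conclusion.

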As many as 52% of healthcare workers in Swiss nursing homes currently have no training or are employed at assistant level and have to cope with the complex needs of people with dementia [33]. Specific knowledge of pain assessment and management in everyday clinical situations in nursing homes with many differently qualified healthcare workers teams is lacking. Consequently this means that the older people suffering from highly complex health problems are cared for by a large number of staff with limited professional knowledge [2]. More specifically, this lack of competency may lead to delayed, improper and inefficient assessments and treatment of medical problems in complex situations such as pain in people with dementia. The largest group of Swiss healthcare workers in nursing homes, 60%, are healthcare assistants and only 27% nursing staff are qualified nurses [33]. It is therefore necessary to provide a communication and information environment that allows healthcare workers at assistant and secondary level to rapidly share observations, accurately and easily with healthcare professionals to initiate decision-making processes. A number of studies of quality of care in nursing home suggest that these measures are inadequately implemented in everyday clinical practice [2, 8, 34, 35]. The research question is therefore: does a nursing-led intervention reduce pain intensity and pain duration for dementia patients living in nursing homes?

Following this research question, the study aim is to identify care needs of people with dementia suffering from pain living in a nursing home. Primary outcomes are pain intensity and pain duration of people with dementia. Secondary outcomes include: differences in pain assessments between healthcare worker groups, behavioural problems, the use of psychopharmacological drugs, and the use of analgesics.

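### Primary hypothesis Ha3 predicts shorter pain-free intervals, which is the direction of harm and runs against the trial's own question

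*Protocol article*

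**What the plan says.** The Protocol article asks in its Background: "does a nursing-led intervention reduce pain intensity and pain duration for dementia patients living in nursing homes". It then names pain intensity and pain duration as the primary outcomes.

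Methods gives three hypotheses for the primary outcomes, each to be judged before versus after the intervention and between groups:

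- Ha1: "There is a 20% reduction in pain events over time before and after the intervention"
- Ha2: "There is a 50% reduction in pain intensity over time before and after the intervention"
- Ha3: "There is a 20% reduction in the duration of pain free intervals over time before and after the intervention"

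Methods also lists pain-free intervals among the measures of the primary outcome. The data analysis text covers pain intensity and duration, "as well as the duration of pain-free intervals with multilevel and events history analyses based on the data observation intervals T0, T1, T2". The Discussion gives the purpose as better pain management and less suffering.

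**The concern.** An intervention that works should leave residents free of pain for longer at a stretch. Ha3 predicts the opposite, while Ha1 and Ha2 beside it predict improvement. Nothing in the article reverses the scale or redefines the interval so that shorter would be better.

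Ha3 is a primary hypothesis, so its direction determines what the trial may report as confirmed. Under the present text, a lengthening of pain-free intervals fails to support Ha3 and a shortening supports it.

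The wrong direction could well appear in the data. Intervention 1 trains staff in systematic pain assessment, so more pain may be recorded and recorded pain-free intervals may shorten. A correction made after such a result was known would look post hoc.

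**Working it through.** **1. The plan's own figure.** Inputs from Methods: "The required number of events for a two-tailed test of individual coefficients within a Cox model", "for a power of 0.8 and a significance level of 0.05", hazard ratio 0.6, covariate SD 0.5, event probability 0.75, drop-out 10%.

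- Events = (1.960 + 0.842)² / (0.5² × (ln 0.6)²) = 120.3, rounded up to 121.
- Persons = 121 / 0.75 / 0.90 = 179.3, stated as 179.

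Both figures reproduce. The 20% in Ha3 does not enter the calculation, so neither its size nor its direction affects the sample size.

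**2. Direction of the three hypotheses.**

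| Hypothesis | Predicted change | Meaning for the resident |
|---|---|---|
| Ha1 | pain events × 0.80 | better |
| Ha2 | pain intensity × 0.50 | better |
| Ha3 | pain-free interval × 0.80 | worse |

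**3. What Ha1 and Ha3 imply together.** Let pain episodes and pain-free intervals alternate over a fixed window, and let f be the share of time free of pain at baseline. The article does not give f, so a range is assumed.

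- Total pain-free time changes by 0.8 × 0.8 = 0.64, a loss of 36%.
- Time in pain becomes 1 − 0.64f, spread over 0.8 times as many episodes.
- Ratio of mean episode length, after to before = (1 − 0.64f) / (0.8 × (1 − f)).

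| Assumed f | Calculation | Episode length ratio |
|---|---|---|
| 20% | 0.872 / 0.64 | 1.36 |
| 50% | 0.680 / 0.40 | 1.70 |
| 80% | 0.488 / 0.16 | 3.05 |

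As f approaches 0 the ratio falls towards 1 / 0.8 = 1.25, and it rises with f. So for any f above 0, both hypotheses can hold only if the average pain episode becomes more than 25% longer.

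**4. What Ha1 implies alone.** If episode length does not change, the ratio of pain-free interval length is (1 − 0.8 × (1 − f)) / (0.8 × f). This gives 2.25, 1.50 and 1.31 for f = 20%, 50% and 80%. Fewer events of unchanged length therefore mean longer pain-free intervals.

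**5. Conditional translation to hazard ratios.** The article does not define the Cox event. If the event is the onset of pain and hazards are constant (two assumptions), the interval ratio is 1 / HR.

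- Ha3 as written: HR = 1 / 0.8 = 1.25.
- Intervals 20% longer: HR = 1 / 1.2 = 0.83.
- Planning HR of 0.6: interval ratio 1 / 0.6 = 1.67, so intervals about 67% longer.

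**The case against.** The best defence is that this is a slip of wording with little effect on the analysis. The Cox coefficient test is two-tailed, so its estimate and p-value are the same whichever direction Ha3 names. The sample size does not use Ha3, and the analysis text sets no directional rule for pain-free intervals. All of this stands, and it limits the point to how a result is interpreted. It does not remove the point, because the error is stated in a primary hypothesis and nothing in the article corrects it. Nor is it an omission that an analysis plan could be expected to fill.

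One might also say that better detection after training would shorten recorded pain-free intervals, so that Ha3 was intended. Ha1 speaks against this, since better detection would also raise the number of recorded events, and Ha1 predicts fewer.

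A reader might infer four stronger things that the article does not support:

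- **That the trial as a whole would succeed if residents got worse.** This is true of Ha3 only. More pain events would fail Ha1, and higher intensity would fail Ha2.
- **That Ha1 and Ha3 are logically incompatible.** They can both hold if episodes lengthen. The conflict is with the aim of shortening pain.
- **That Ha3 contradicts the planning hazard ratio of 0.6.** That requires pain onset as the event. If the event were the end of a pain episode, a hazard ratio below 1 would mean longer pain.
- **That the authors certainly meant an increase.** They may equally have meant the duration of pain. The Background names it as a primary outcome, no primary hypothesis covers it, and that reading would keep both the verb and the 20%.

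**Conclusion.** The point holds as an internal contradiction in a primary hypothesis. Ha3 as written is supported by deterioration and not by improvement. It opposes the research question, the purpose given in the Discussion and the direction of Ha1 and Ha2.

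The contradiction of direction rests on the text alone and needs no assumption. The size of the conflict with Ha1 (episodes about 1.4 to 3.1 times as long) depends on the assumed range of baseline pain-free time and on episodes and intervals alternating over a fixed window. The hazard ratio comparison depends on the two assumptions named in the working and is illustrative only.

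No planned test or sample size figure becomes wrong. The matter still needs correction before analysis, because it decides what may be claimed for a primary hypothesis.

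**What to change.** Before any outcome is analysed, the investigators should say which quantity Ha3 was meant to address and amend it in one of two ways:

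- an increase in the length of pain-free intervals, with the size confirmed; or
- a reduction in how long pain lasts, if pain duration was meant.

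The same amendment should define the event in the Cox model and say which direction of the hazard ratio means benefit. If pain onset is chosen and 20% longer intervals is the target, the corresponding hazard ratio under constant hazards is about 0.83, and this can be stated beside the planning value of 0.6.

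The cost is one reworded sentence and one added definition. The direction correction itself changes no data collection and no sample size. The amendment should be dated so that the direction is seen to be fixed before results are known.

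### The event calculation assumes a hazard ratio of 0.6, which the article does not reconcile with the 20% changes in H_a1 and H_a3 that the sample is said to test

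*Protocol article*

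**What the plan says.** Everything here is in the Methods of the protocol article.

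- **Hypotheses.** H_a1 reads "There is a 20% reduction in pain events over time before and after the intervention", and also between the intervention and comparison groups. H_a3 states a 20% change in the length of pain-free intervals, worded as a reduction. H_a2 states a 50% reduction, but in pain intensity, which is a score and not a time to an event.
- **Link to sample size.** The sentence after the hypotheses says that the sample size follows from what the event history and multilevel analyses need in order to test them.
- **Event calculation.** It concerns "The required number of events for a two-tailed test of individual coefficients within a Cox model with other covariates". The result is 179 people and 121 events, which "are required for a power of 0.8 and a significance level of 0.05 based on an expected hazard ratio of 0.6 (SD 0.5". The event probability is 0.75 and drop-out is 10%. The paragraph ends: "Both the number of people and the number of events determined in the intended study protocol can be collected".
- **Outcome scale.** Pain events are counted by shift and by week.
- **Planned sample.** The total is 411 residents. The comparison home contributes 150.

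**The concern.** A hazard ratio of 0.6 is a 40% lower hazard. The hypotheses that bear on event occurrence state 20%. The article prints both figures close together and says that the calculation serves the hypotheses, yet it gives no step from one to the other.

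The size of the assumed effect drives the result, because the number of events needed varies with the inverse square of the log hazard ratio. If 20% means a hazard ratio near 0.8, the stated 80% power does not apply to H_a1 or H_a3. A null result could then be taken as evidence against a 20% reduction from a trial described as adequately powered to find one.

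**Working it through.** **Inputs from the Methods:** two-sided alpha 0.05; power 0.80; hazard ratio (HR) 0.6; covariate SD 0.5 (a two-group variable split 1:1); event probability 0.75; drop-out 10%; total 411, of whom 150 are comparison residents, leaving 411 − 150 = 261.

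**Formula (Hsieh and Lavori):** D = (1.960 + 0.842)² / (SD² × ln(HR)²). People = D / 0.75 / 0.90.

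**1. The plan's own figure.** At HR 0.6, D = 7.849 / (0.25 × 0.2609) = 120.3, so 121 events. People = 120.3 / 0.75 / 0.90 = 178.2, so 179. Both match. HR 0.6 is therefore the value actually used, with one event probability per person.

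**2. 20% as a rate reduction.** With a constant hazard, a 20% lower rate is HR 0.8. D = 7.849 / (0.25 × 0.04979) = 630.5, so 631 events. People = 631 / 0.75 / 0.90 = 934.8, so about 935.

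For H_a3, an interval 20% shorter gives HR 1 / 0.8 = 1.25, which has the same absolute log and so the same power as 0.8. An interval 20% longer gives 1 / 1.2 = 0.833, and power is lower than shown below.

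**3. Power for HR 0.8.** Power = Φ(√D × SD × |ln HR| − 1.96). With 411 residents at one event each, D = 411 × 0.75 = 308 without drop-out and 308 × 0.90 = 277 with it. At a 150:261 split, SD = √(0.365 × 0.635) = 0.481.

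| Events | Split | Power at HR 0.8 | HR detectable with 80% power |
|---|---|---|---|
| 121 | 1:1 | 23% | 0.60 |
| 277 | 150:261 | 43% | 0.70 |
| 277 | 1:1 | 46% | 0.71 |
| 308 | 150:261 | 47% | 0.72 |
| 308 | 1:1 | 50% | 0.73 |

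None of these rows allows for clustering within four homes.

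**4. 20% as a fall in the proportion with any pain event.** With a constant hazard, HR = ln(1 − p_intervention) / ln(1 − p_comparison). The answer depends on which group the 0.75 describes.

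| Where 0.75 sits (20% relative fall) | Proportions | HR | Events for 80% power |
|---|---|---|---|
| Comparison group | 0.75 to 0.60 | 0.66 | 184 |
| Average of both groups | 0.833 to 0.667 | 0.61 | 132 |
| Intervention group | 0.9375 to 0.75 | 0.50 | 66 |

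A fall of 20 percentage points, from 0.75 to 0.55, gives HR 0.58 and 104 events.

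**The case against.** - **Some readings come close to 0.6.** The last table in the working shows this, and the calculation does rest on a per-person event probability. This stands: a reader who infers that 0.6 cannot be obtained from 20% goes too far. But the article does not state a proportion reading, and an outcome counted by shift and week fits a rate better.
- **The planned sample is 411, and pain recurs.** Residents are observed over three cycles of 49 days. At HR 0.8 the need is 631 events at 1:1, or 681 at 150:261, which is only 1.5 to 1.7 per resident. So neither 23% nor 43% to 50% is the trial's actual power. That stands too. Adequacy is still not shown: the stated calculation counts one event per person, repeated events in one resident are correlated, and clustering reduces the information further.
- **The Cox model is not assigned to H_a1 by name.** The analysis paragraph applies multilevel and event history methods to intensity, duration and pain-free intervals, so H_a3 is the clearer link. H_a1 also contains a before-after comparison, which the two-group formula does not describe. This limits how far the figures describe the H_a1 test. It does not remove the statement that the sample was sized for the hypotheses.
- **This is a condensed article.** A reason for 0.6 may be in the full protocol. But both numbers, and the claim that joins them, are printed here.

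**Conclusion.** The point holds as a failure to reconcile two printed effect sizes. The arithmetic itself is correct. Read as a rate reduction, the 20% in H_a1 and H_a3 corresponds to a hazard ratio of about 0.8. The formula then asks for 631 events instead of 121. Power is 23% at 121 events and about 43% to 50% at one event per person in all 411 residents, where the detectable hazard ratio is about 0.70 to 0.73. These figures assume a constant hazard, the stated 0.75 event probability, drop-out between 0 and 10%, and no clustering loss.

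Two stronger conclusions are tempting and not supported. One is that all the primary hypotheses claim 20%; H_a2 claims 50%, on a different kind of outcome. The other is that the trial's real power for a 20% effect is known to be far below half. That figure belongs to the 121-event minimum, and the article does not give enough on recurrent events, clustering or the proportion reading to settle the power of the planned 411.

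**What to change.** Do one of the following:

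1. State how the 20% in H_a1 and H_a3 translates into a hazard ratio (rate, interval length or proportion affected; relative or absolute; and which group the 0.75 describes). Then restate the power, or the hazard ratio detectable with 80% power, for the planned 411 on that basis.
2. Align H_a1 and H_a3 with a hazard ratio of 0.6 and give the reason for that value.

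If recurrent pain events are to be counted, base the restated power on that model instead of on one event per person. Do so only where the historical comparison data hold the same event records. The Methods leave this unclear: the primary outcome is said to be measured by shift and week in both groups, but the comparison is described as using the first and 49th day of each phase and the last documented assessment.

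No residents need to be added. The cost is a recalculation and some wording. On the rate reading at one event per person, the stated power becomes less favourable.
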